## Abstract

**Introduction:**

Adolescent idiopathic scoliosis (AIS) is a three-dimensional spinal deformity that can impair posture, function, and quality of life. Schroth exercise, a physiotherapeutic scoliosis-specific exercise, has demonstrated benefits in reducing Cobb angle and improving patient-reported outcomes. Traditional Chinese Medicine (TCM) manipulation may modulate musculoskeletal asymmetry and pain, potentially exerting synergistic effects when combined with Schroth therapy. This study aims to evaluate whether TCM manipulation plus Schroth exercise is superior to Schroth exercise alone in improving spinal curvature, patient-centered outcomes, and paraspinal symmetry in AIS.

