**Methods:**

This is a single-center, randomized controlled, two-arm parallel-group superiority trial. Sixty adolescents (aged 10–18) with idiopathic scoliosis and Cobb angle 10°–45° will be randomized 1:1 to: (1) Schroth therapy alone (control) or (2) TCM manipulation combined with Schroth exercise (intervention). Primary outcome is change in Cobb angle measured by full-length standing anteroposterior spinal radiograph before and after the intervention. Secondary outcomes include Angle of Trunk Rotation (ATR), paraspinal thermal asymmetry assessed by infrared thermography, and health-related quality of life measured by the Scoliosis Research Society-22r (SRS-22r) questionnaire. Participants will be randomly allocated (1:1) using a computer-generated, stratified block randomization sequence with allocation concealed by sealed opaque envelopes. The analysis will follow the intention-to-treat (ITT) principle, and an ANCOVA adjusting for baseline measurements will be used for between-group comparisons. A total sample size of 60 participants (30 per group) was determined *a priori* to provide 80% power (*α* = 0.05, *β* = 0.20) to detect a clinically meaningful difference in Cobb angle, allowing for a 20% attrition rate.

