#### TCM manipulation and Schroth therapy

2.3.1

Participants in the intervention group will receive standardized TCM manipulation immediately before each supervised Schroth session during the initial 2-week inpatient phase. Both interventions will be delivered twice daily, five days per week: Schroth sessions will last approximately 2 h, and each TCM manipulation will last approximately 30 min. The TCM protocol is standardized to ensure reproducibility and delivered by licensed practitioners with over five years of clinical experience. Techniques target paraspinal soft tissues, acupoints along the Bladder Meridian, and spinal mobilization, aiming to reduce myofascial tension, enhance segmental mobility, and facilitate three-dimensional postural correction (Table 2, Figure 2).

**Table 2 T2:** TCM manipulation.

Step	Manipulation Technique	Procedure Description
1	*Gunfa* (Rolling) and *Zhang Roufa* (Palm Kneading)	Patient in prone position. Apply rolling and palm kneading to the muscles along the Bladder Meridian of the back and the *Jiaji* region, moving back and forth several times. Palpate for *jingbi* (tender/obstructed) points. Use *Roubo Fa* (kneading and plucking) to relax tense muscles; use rolling and palm kneading on soft or weak musculature. Duration: ∼10 min.
2	*Yizhichan Tuifa* (One-finger Zen Pushing) with *Zhi Roufa* (Finger Kneading)	Based on syndrome differentiation, select acupoints such as *Feishu* (BL13), *Xinshu* (BL15), *Ganshu* (BL18), *Pishu* (BL20), *Weishu* (BL21), *Shenshu* (BL23), *Dachangshu* (BL25). Push along the point using the one-finger Zen technique, pausing at each point for finger kneading 1–2 min, until a tolerable aching/distending sensation occurs. Duration: ∼5 min.
3	*Zhang Ca Fa* (Palm Rubbing) and *Niejifa* (Spinal Pinching)	Apply a small amount of Vaseline or similar medium along the *Du Mai* (Governor Vessel), *Jiaji*, and Bladder Meridian areas. Perform palm rubbing in straight, back-and-forth movements until the skin is slightly red and warm, then pinch along the spine for 3–5 passes.
4	Rhythmic Spinal Oscillation	Place one palm over the cervicothoracic junction or a selected spinal segment for stabilization, and the other palm on the lumbosacral midline. Using the spine as the axis, both palms work together to rhythmically oscillate the spine and pelvis, gradually increasing amplitude within patient tolerance.

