### Outcomes

2.6

To minimize radiographic exposure, outcome measures will be assessed at different timepoints based on their invasiveness and clinical practicality. All outcomes will be assessed at baseline (week 0) and study completion (week 12). Additionally, to capture the immediate effects of the intensive inpatient intervention, all secondary outcomes will also be assessed immediately following the 2-week intensive intervention period (week 2).

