#### Secondary outcomes

2.6.2

Angle of Trunk Rotation (ATR), will be measured by a trunk rotation measurement device (weeks 0, 2, and 12). Axial trunk rotation (ATR) was measured using a Bunnell scoliometer (Hengjian Medical Technology Co., Ltd., Zhengzhou, China). Participants performed the forward-bending Adams test. The trunk rotation angle was systematically measured at the thoracic, thoracolumbar, and lumbar levels, and the values for each segment were recorded separately (14). A minimum of two measurements were taken for each segment per participant, and the average value was calculated and used to improve accuracy. All ATR measurements were performed by the same trained assessor.

Paraspinal surface temperature difference (ΔT) between convex and concave sides will be assessed via infrared thermography at standardized anatomical regions, including the trapezius, latissimus dorsi, and quadratus lumborum muscles (weeks 0, 2, and 12). Imaging will be performed using a short-focus uncooled far-infrared thermographic camera (Baotonghua Medical Equipment Co., Ltd., Chongqing, China). The examination room will be maintained at a constant temperature of 24 ± 2 °C with no drafts. The camera will be actived for 15 min prior to each session. Participants will acclimatize for 15 min while adopting a standardized standing posture (back to camera, head slightly lowered, feet shoulder-width apart, arms slightly abducted). Black body calibration will be performed prior to each participant. The *Δ*T for each muscle will be calculated by subtracting the mean concave-side temperature from the convex-side temperature.

Health-related quality of life, evaluated using the Society-22r(SRS-22r) questionnaire (weeks 0, 2, and 12).

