### Statistical analysis

2.9

All analyses will be conducted using SPSS (version 20.0, SPSS Inc., Chicago, IL, USA) with a two-sided significance level of *α* = 0.05. All analyses will follow the intention-to-treat(ITT) principle. Baseline characteristics will be summarized descriptively. The primary outcome, change in Cobb angle from baseline to week 12, will be compared between groups using Analysis of Covariance (ANCOVA), adjusting for the baseline Cobb angle. Results will be presented as adjusted mean differences with 95% confidence intervals. For secondary outcomes measured at multiple timepoints (ATR, ΔT, SRS-22r), linear mixed-effects models (LMMs) will be used to analyze the longitudinal data. The models will include fixed effects for time, group, and their interaction term, with participant as a random effect. The interaction effect will be examined to test if the change over time differs between groups.

Given the multiple secondary outcomes, we will control for multiple comparisons using the False Discovery Rate (FDR) approach (Benjamini-Hochberg procedure) across the secondary endpoints. Secondary outcome *p*-values will be adjusted using FDR at the 5% level to mitigate Type I error inflation. We will treat these analyses as exploratory; any inferences from secondary outcomes will be made with caution.

Missing data will be handled under the missing-at-random assumption using full information maximum likelihood (FIML) in the mixed-effects models. A multiple imputation approach will be performed as a sensitivity analysis to verify the robustness of results.

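### Thermal asymmetry is analysed as a signed convex-minus-concave difference, whose mean does not reliably measure the stated aim of paraspinal symmetry

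*Protocol article*

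**What the plan says.** The abstract gives the objective as superiority in "improving spinal curvature, patient-centered outcomes, and paraspinal symmetry in AIS" and names the secondary outcome "paraspinal thermal asymmetry assessed by infrared thermography". Both describe closeness of the two sides, with zero difference as the ideal.

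Section 2.6.2 sets the measurement. It covers standardised regions "including the trapezius, latissimus dorsi, and quadratus lumborum muscles (weeks 0, 2, and 12"), and ΔT "for each muscle will be calculated by subtracting the mean concave-side temperature from the convex-side temperature". The result is a signed number. No absolute value, expected sign or direction of benefit is given.

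Section 2.9 puts ΔT, with ATR and SRS-22r, into linear mixed models: "The models will include fixed effects for time, group, and their interaction term, with participant as a random effect". The interaction is the test of interest. Secondary p-values are FDR-adjusted and these analyses are called exploratory.

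On timing, section 2.6 has secondary outcomes "assessed immediately following the 2-week intensive intervention period (week 2") as well as at weeks 0 and 12. Section 2.3.1 says of manipulation and Schroth therapy: "Both interventions will be delivered twice daily, five days per week". Manipulation is given only in the intervention arm, before each Schroth session. Step 3 of Table 2 reads "Perform palm rubbing in straight, back-and-forth movements until the skin is slightly red and warm". The imaging procedure asks for 15 minutes of acclimatisation and states no interval since the last session.

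**The concern.** Symmetry is distance from zero. A signed difference also carries direction, and a group-by-time test on its mean responds to a shift in direction. The two coincide only under conditions that the article does not state.

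There are two ways to go wrong. If some participants are warmer on the convex side and others on the concave side, equal gains in symmetry move their signed values in opposite directions and cancel in the mean. And if a participant passes through zero to an equal difference on the other side, the signed value changes a great deal while symmetry does not change at all.

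At stake is the reading of an outcome that the Discussion presents as part of the study's innovation and as a possible physiological correlate of clinical change. A null result could hide a real gain, and a positive result could reflect reversal.

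A smaller point concerns week 2. Only one arm has its skin rubbed warm during the inpatient phase, and the time from the last session to imaging is not fixed. Residual warmth could enter the week-2 contrast if it differs between the two sides of the back.

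**Working it through.** The article states no figure for ΔT (no mean, SD, expected effect or power), so there is nothing to reproduce. The check is one of logic, with illustrations.

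**Single participants**
- From +0.4 to +0.2 °C: signed change −0.2, change in |ΔT| −0.2.
- From −0.4 to −0.2 °C: signed change +0.2, change in |ΔT| −0.2. Averaged with the first participant, the signed change is 0 although both asymmetries halved.
- From +0.4 to −0.4 °C: signed change −0.8, change in |ΔT| 0.

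**Illustration A: normally distributed baseline difference**

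Assumptions, none from the article: true ΔT ~ N(μ, SD 0.5 °C); independent noise with SD 0.2 °C at each visit; the intervention multiplies each true difference by 0.5; no change in control. From the article: 25 analysable per arm (section 2.7) and two-sided α = 0.05. The test is a t-test on change.

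The signed analysis has a closed form:
- Between-arm difference in mean change = −0.5μ.
- Variance of change, control: 2 × 0.2² = 0.08. Intervention: 0.5² × 0.5² + 0.08 = 0.1425.
- SE = √[(0.08 + 0.1425)/25] = √0.0089 = 0.0943.
- μ = 0: ratio 0, so power equals α, 5%.
- μ = 0.3: 0.15/0.0943 = 1.59, power about 34–35%.
- μ = 0.5: 0.25/0.0943 = 2.65, power about 74%.

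Simulation supplies the absolute analysis:

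| Mean baseline ΔT | Power, signed | Power, absolute |
|---|---|---|
| 0 °C | 5% | 62% |
| 0.3 °C | 35% | 74% |
| 0.5 °C | 74% | 90% |

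Repeat runs move these by about one percentage point.

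**Illustration B: a varying share q of participants with the convex side warmer**

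Assumptions: baseline |ΔT| 0.5 °C (SD 0.15), noise SD 0.15 °C, asymmetry halved in the intervention arm, 25 per arm. The expected signed difference is −0.25 × (2q − 1).

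| q | Mean difference, signed | Mean difference, absolute | Power, signed | Power, absolute |
|---|---|---|---|---|
| 1.0 | −0.25 | −0.24 | 97% | 97% |
| 0.9 | −0.20 | −0.24 | 80% | 98% |
| 0.8 | −0.15 | −0.24 | 51% | 97% |
| 0.7 | −0.10 | −0.24 | 25% | 97% |
| 0.5 | 0.00 | −0.24 | 5% | 97% |

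With a 30% reduction in place of 50%, signed versus absolute power is 67% vs 67% at q = 1.0, 28% vs 69% at q = 0.8 and 4% vs 67% at q = 0.5.

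**The opposite error**

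With the distributions of illustration A, let the intervention only reverse each participant's sign, so that symmetry is unchanged. The signed test is then significant in 77–79% of runs at μ = 0.3 °C and in over 99% at μ = 0.5 °C. The absolute test stays at 5%. A full reversal is an extreme case, used only to show that the signed test answers a different question.

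**Timing**

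The week-2 image is tied to the end of the two-week period, not to a session. Each manipulation is followed by a Schroth session of about 2 hours, so if the last session runs as described, at least that time plus 15 minutes of acclimatisation separates rubbing from imaging. Writing the added warmth as w on the convex side and v on the concave side, the effect on ΔT is w − v, which is zero if both sides warm equally. Table 2 names no side for the rubbing. Step 1 does treat tense and weak muscle differently, so unequal warming is possible but not shown. No manipulation is given in the home phase, so week 12 falls about 10 weeks after the last one.

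**The case against.** The strongest reply is that ΔT is not an arbitrary left-minus-right difference. It is aligned to the deformity, so its sign has a common meaning. If one side is consistently warmer and nobody overshoots, the signed mean tracks symmetry. That stands: at q = 1.0 the two analyses have the same power, and at a mean of 0.5 °C the signed one still reaches 74%. A reader might infer that the signed outcome cannot show improvement in symmetry at all, but that is too strong. What remains is that the article neither states nor supports the condition on which the signed analysis depends.

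A second reply is that derivations are often left to the full protocol or SAP. Here, however, the article itself fixes the formula and the model, and they do not match the aim it states. Nor is information lost, since |ΔT| can be computed from the recorded values.

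Three further readings are tempting, and the text does not support them:
- That one convex/concave label is applied to all three muscles in double curves. The definition is per muscle, which allows sides to be set by level; the major-curve rule in section 2.6.1 belongs to the Cobb angle. The article simply does not say how sides are assigned.
- That skin warming undermines the outcome as a whole. It can concern week 2 only, after an intervening Schroth session, and only if the two sides warm unequally.
- That reddened skin unblinds the thermography assessor. Table 2 describes slight redness, and about 2 hours of exercise follow, so this is speculation.

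Finally, the outcome is secondary and exploratory, and no power was claimed for it. That limits the weight of the point but does not repair the definition.

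**Conclusion.** The concern holds in a limited form. The analysed quantity is a signed mean, the stated aim is closeness to zero, and the two agree only if participants share a baseline sign and do not overshoot. Otherwise the analysis can miss a real gain or count a reversal as change.

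How much this matters depends on a distribution that the article does not give. In the illustrations, the loss of power from using the signed value runs from none (97% vs 97%, all of one sign) to nearly complete (5% vs 62% or 5% vs 97%, signs evenly split). These figures show a mechanism under assumed SDs and effects; they do not predict this trial's power.

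The open interval before week-2 imaging is a minor addition, confined to that visit. The primary outcome, change in Cobb angle, is not affected.

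**What to change.** Before unblinding, state that |ΔT| per muscle is the analysed symmetry endpoint, with a reduction as the direction of benefit. Report signed ΔT descriptively, and say that convex and concave sides are set by the curve at each muscle's level. Fixing this beforehand matters because a choice between signed and absolute made after seeing the arms would be data-driven.

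The cost is one definition line; values already recorded can be recomputed. The downside is that |ΔT| is skewed near zero, which a transformation or robust standard errors can handle.

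As a minor addition, add one line that week-2 thermography is taken at the same stated interval from the last session in both arms. This changes assessment timing only. Images already taken cannot be re-timed, so for those the actual interval should be reported where it is known.

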### Sample size

2.7

The sample size was determined *a priori* using G*Power software (version 3.1.9.7). Based on the primary outcome of change in Cobb angle, an effect size of 0.81 was derived from a previous randomized controlled trial (15). This effect size corresponds to a between-group difference of approximately 4°–5° in Cobb angle improvement. We consider this difference clinically meaningful as it exceeds both the typical measurement error (∼3°) and the established minimal clinically important difference (MCID) of 3.5° for non-operative interventions in AIS (16). The calculation was performed for a two-tailed independent-samples *t*-test, with an alpha (α) error level set at 0.05 and a beta (β) error level set at 0.20 (statistical power of 80%). The result indicated that a total of 50 participants (25 per group) would be required to detect the anticipated effect. To account for a potential attrition rate of approximately 20% throughout the trial period, the target sample size was increased to 60 participants (30 per group) to ensure adequate statistical power for the final analysis.

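### Sixty randomised less 20% attrition leaves 48, below the 50 evaluable participants the protocol requires for 80% power

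*Protocol article*

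**What the plan says.** Section 2.7 (Sample size) uses G*Power with a two-tailed independent-samples *t*-test, α = 0.05, 80% power and a standardised effect of 0.81 taken from an earlier randomised trial. It reports that "a total of 50 participants (25 per group) would be required to detect the anticipated effect". It then assumes attrition of about 20% and concludes that "the target sample size was increased to 60 participants (30 per group) to ensure adequate statistical power for the final analysis".

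The Methods paragraph of the abstract makes the same claim more firmly. It says that 60 participants, 30 per group, were chosen to give 80% power "to detect a clinically meaningful difference in Cobb angle, allowing for a 20% attrition rate". There the attrition rate carries no word such as *approximately*.

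**The concern.** An attrition allowance should leave the required number of evaluable participants after the assumed losses. The losses come out of the number randomised, so the requirement must be divided by one minus the attrition rate. Here 60 is what results from adding 20% of the requirement to the requirement. If so, the enrolled number falls short at exactly the attrition rate it was meant to cover.

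What is at stake is a planning statement that appears in both the abstract and section 2.7 and is likely to be carried into the results report. The sample size, the analysis and the type I error are not affected.

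**Working it through.** **Inputs, all from the protocol article**

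- Effect size d = 0.81, two-sided α = 0.05, target power 80%, two-sample *t*-test (section 2.7)
- 1:1 allocation (abstract, Methods)
- Evaluable requirement 50, 25 per group (section 2.7)
- Attrition about 20% (section 2.7) or 20% (abstract)
- Number randomised 60, 30 per group (both places)

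**Step 1. Reproduce the 50.** With n per group, the test statistic under the alternative follows a noncentral *t* distribution with 2n − 2 degrees of freedom and noncentrality d × √(n/2). Power is the probability that its absolute value exceeds the two-sided 5% critical value.

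| n per group | df | noncentrality | critical value | power |
|---|---|---|---|---|
| 24 | 46 | 0.81 × √12 = 2.806 | 2.013 | 78.4% |
| 25 | 48 | 0.81 × √12.5 = 2.864 | 2.011 | 80.1% |
| 30 | 58 | 0.81 × √15 = 3.137 | 2.002 | 87.0% |

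The smallest n reaching 80% is 25 per group, so the protocol's 50 reproduces exactly.

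**Step 2. Apply the stated attrition to the stated target.** 60 × (1 − 0.20) = 48, or 24 per group if losses are even. That is two below the requirement, and the table gives 78.4% power. The difference from 25 per group is 80.1 − 78.4 = 1.7 points.

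**Step 3. Allow for uneven losses.** With the same 48 completers, a 22/26 split gives 78.2% and a 20/28 split gives 77.3%. If each participant drops out independently with probability 0.20, power averaged over the possible outcomes is 78.1%, and the chance that at least 50 of 60 remain is 32%.

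**Step 4. Find the number that would meet the claim.** In total, 50 / (1 − 0.20) = 62.5, so 63. By arm, 25 / 0.80 = 31.25, so 32 per arm and 64 in total. As a check, 64 × 0.80 = 51.2, which is above 50.

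**Step 5. Find the attrition that 60 can bear.** 1 − 50/60 = 16.7%, which is 10 losses. Twenty per cent of 60 is 12.

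**Step 6. Likely source.** 50 × 1.2 = 60 exactly, whereas 50 / 0.80 is not 60. The protocol does not print this step, so the source is an inference. The conclusion does not need it, because Step 2 is enough.

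**The case against.** Four arguments can be made for leaving the text alone.

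- **The inputs are rough.** Section 2.7 speaks of approximately 20% attrition and promises only adequate power after inflation. At 24 per group, an effect of about 0.826 instead of 0.81 would restore 80%. This softens the wording of section 2.7, but the abstract states 20% and 80% flatly, and 16.7% is the most that 60 can cover.
- **The planned ANCOVA may recover the loss.** Section 2.9 adjusts for baseline Cobb angle, while the calculation is for an unadjusted *t*-test. Dividing d by √(1 − r²), where r is the correlation between baseline and change, power at 24 per group is 78.8% for r = 0.1, 80.1% for r = 0.2, 82.1% for r = 0.3 and 88.7% for r = 0.5. These values of r are assumptions. The protocol gives no correlation and claims no such gain, so the argument could support a new calculation but does not support the one printed.
- **Not every drop-out loses the primary outcome.** Section 2.8 continues data collection after discontinuation where possible. However, an attrition allowance in a sample size calculation stands for participants without usable outcome data, and section 2.7 gives it no other meaning.
- **A normal approximation needs only 24 per group** (80.1%). The protocol names G*Power and a *t*-test, and its 25 per group is the *t*-based figure.

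What stands is that the matter is small and that actual power may well be adequate. None of this makes 60, 20% and 80% consistent on the stated calculation.

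**Conclusion.** The point holds as a minor arithmetic correction. The 50 is right and 60 is a workable target; the error is in the attrition rate attached to it. On the protocol's unadjusted *t*-test at d = 0.81 with even losses, 20% attrition gives 78.4% power, so the design misses its stated 80% by about 1.6 points and its own evaluable requirement by two participants. The target is met only if no more than 10 of the 60 are lost. The validity of the trial is not in question.

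**What to change.** Correct section 2.7 and the abstract in the same way, using one of two statements:

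- 60 participants retain 80% power with up to 16.7% attrition (10 participants); or
- 60 participants with 20% attrition leave 48 evaluable, giving about 78% power at an effect size of 0.81 on an unadjusted *t*-test.

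If the team would rather keep the claim of 80% power at 20% attrition, the matching target is 64 (32 per group), four more than planned. That is not necessary given the size of the shortfall. If the team wishes to rely on the gain from baseline adjustment, the assumed correlation and its source should be stated.

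The cost of the first two options is two sentences and a slightly less favourable planning figure. Enrolment, analysis and conduct stay as they are.
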